### Number of patients

The run-in phase Ib part (see section below) will include 6(3+3) patients. These 6 patients will also be part of stage I of the trial (n=22). In case 3 or more patients are free of progression at 6 months, an additional 18 patients will enter the trial. A total of 40 patients will participate (n=40).

## 4.2 Dose limiting toxicity

Until now, atezolizumab has not been administered with carboplatin AUC1.5. Though in advanced NSCLC, no DLTs were observed in patients treated with nivolumab (anti-PD1) plus carboplatin/paclitaxel [24]. The safety and efficacy of atezolizumab in combination with carboplatin AUC6 (and nab-paclitaxel) is currently being investigated (NCT01633970) in metastatic breast cancer patients. Currently, at the NKI in a phase I study (N16LOG) the safety of carboplatin (AUC5)/cyclophosphamide/atezolizumab is assessed. Pending these results, special safety assessments will be performed on the first 6 (3+3) patients entering this GELATO trial (phase I, run in). Based on the well-known toxicity profiles of both carboplatin and atezolizumab, we don't expect significant toxicity using the combination treatment.

In order to monitor unexpected toxicity related to the use of atezolizumab in combination with carboplatin AUC1.5, dose-limiting toxicities (DLTs) will be scored during the first 5 weeks of treatment (DLT window). In case in the first 3 patients 1 DLT is observed, another 3 patients will be included. In case in this group a second DLT is seen (2/6), the investigators will report this to Roche as well as to the Institutional Review Board (IRB). Together with Roche and the IRB the protocol committee will discuss whether patients can still be entering the trial or whether the trial needs to be re-designed with regard to dose or inclusion criteria.

The following adverse events are considered DLTs:

**DLT is defined as grade 4 or 5 toxicity according to CTCAE 4.03, or grade 3 persisting for 6 weeks and these toxicities cannot be attributed to progression of disease**

Hematological toxicities defined as:

- Grade 4 neutropenia (ANC  $<0.5 \times 10^9/l$ ) lasting  $\geq 14$  days
- Grade  $\geq 3$  febrile neutropenia
- Grade 4 thrombocytopenia lasting  $\geq 48$  hours
- Grade  $\geq 3$  thrombocytopenia associated with clinical significant bleeding episodes

Non-hematological toxicity  $\geq 3$  including:

- Grade 3 hyperbilirubinemia lasting for  $> 48$  hours or any Grade 4 hyperbilirubinemia
- Grade  $\geq 3$  AST/ALT elevations with hyperbilirubinemia of  $\geq$  grade 2
- Grade 4 AST/ALT elevations
- For patients with Grade 2 AST/ALT, and/or alkaline phosphatase abnormality at baseline, an increase to  $\geq 10 \times$  the upper limit of normal (ULN) that does not resolve to Grade  $\leq 2$  within 48 hours (if symptomatic) or that does not resolve to Grade  $\leq 1$  within 3 weeks of onset (if asymptomatic) will be considered a DLT after AST/ALT elevation due to disease progression has been ruled out
- Grade  $\geq 3$  pneumonitis
- Grade  $\geq 3$  colitis

Failure to recover from any toxicity that results in a delay of 2 scheduled administrations of atezolizumab is considered a DLT. The following are not considered DLTs:

- Grade  $\geq 3$  nausea, vomiting, or diarrhea that resolves to Grade  $\leq 1$  with or without treatment prior to the next infusion

- Grade  $\geq 3$  immune-related adverse event that resolves to Grade  $\leq 1$  with immunosuppressant therapy within 3 weeks of its onset
- Grade  $\geq 3$  fatigue that resolves to Grade  $\leq 2$  within 1 week
- Grade  $\geq 3$  arthralgia that can be adequately managed with supportive care or that resolves to Grade  $\leq 2$  within 1 week
- Grade  $\geq 3$  hypophosphatemia reversible to  $<$  Grade 2 within 1 week
- Grade  $\geq 3$  laboratory abnormality that is asymptomatic and deemed by the investigator not to be clinically significant
- Grade  $\geq 3$  autoimmune thyroiditis or other endocrine abnormality that can be managed by endocrine therapy or hormonal replacement
- Grade  $\geq 3$  tumor flare defined as local pain, irritation, or rash localized at sites of known or suspected tumor
- Alopecia (any grade)
- Infusion related reactions (IRRs): IRRs are not considered to be DLTs because based on experience with monoclonal antibodies; IRRs are not dose-related events. Precautions will be taken if IRRs Grade  $\geq 2$  occurs. If described precautions are not sufficient, other options will be discussed between the sponsor and the investigator.

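### Section 4.2 defines a DLT in conflicting ways, includes two criteria that outlast the 5-week window, and words the 2/6 trigger for only one path

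*Protocol*

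**What the plan says.** All of this is in Protocol Section 4.2 unless noted.

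- **Window.** "dose-limiting toxicities (DLTs) will be scored during the first 5 weeks of treatment (DLT window".
- **Definition.** In bold: "DLT is defined as grade 4 or 5 toxicity according to CTCAE 4.03, or grade 3 persisting for 6 weeks", provided the toxicity is not attributable to disease progression. The synopsis (special safety assessments) gives this rule and refers to Section 4 for the rest.
- **List under the definition.** Grade 4 neutropenia counts if it lasts at least 14 days and grade 4 thrombocytopenia if it lasts at least 48 hours. Febrile neutropenia of grade 3 or more counts. So does non-hematological toxicity of grade 3 or more, including pneumonitis, colitis, grade 3 bilirubin beyond 48 hours and grade 4 AST/ALT.
- **Delay criterion.** "Failure to recover from any toxicity that results in a delay of 2 scheduled administrations of atezolizumab is considered a DLT".
- **Exceptions.** Events that are not DLTs include a grade 3 or higher immune-related event that settles to grade 1 or less with immunosuppressants within 3 weeks, and a grade 3 or higher "laboratory abnormality that is asymptomatic and deemed by the investigator not to be clinically significant".
- **Trigger.** "In case in the first 3 patients 1 DLT is observed, another 3 patients will be included". Then: "In case in this group a second DLT is seen (2/6), the investigators will report this to Roche" and to the IRB, followed by a discussion of whether accrual can continue or the trial must be redesigned.
- **Elsewhere.** Section 4.1 (number of patients) and Section 9.2 plan six run-in patients without a condition. Section 9.6 (stopping rules) only refers back to Section 4.

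**The concern.** The run-in produces one number, the count of DLTs among six patients, and that number decides whether the trial is referred for discussion. If two sentences of the same section classify one event differently, sites can reach different counts from the same patients. If a criterion takes longer than the window, a patient's status at the end of the window is provisional, and the text does not say so. If the action is tied to one order of events, the same total of two DLTs may or may not lead to a report. This matters because the section itself says that atezolizumab has not been given with carboplatin at AUC 1.5, and because Section 9.6 names this text as the stopping rule.

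**Working it through.** **1. Plan's own figures.** The protocol states no probability for the run-in, so there is nothing to reproduce there. The Simon design does reproduce. Summing P(X1 = x) × P(X2 ≥ 8 − x) over x = 3 to 22, with X1 from 22 patients and X2 from 18, gives 0.0398 at a true proportion of 10% (stated 0.04) and 0.803 at 25% (stated 80%).

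**2. Definitions side by side** (events not attributable to progression).

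| Event | Bold rule | List | Exceptions |
|---|---|---|---|
| Grade 4 neutropenia, under 14 days | DLT | not met | – |
| Grade 4 thrombocytopenia, under 48 hours, no significant bleeding | DLT | not met | – |
| Grade 3 febrile neutropenia, under 6 weeks | not met | DLT | – |
| Grade 3 immune-related colitis or pneumonitis, settled within 3 weeks on immunosuppressants | not met | DLT | not a DLT |
| Grade 4, otherwise as in the row above | DLT | DLT | not a DLT |
| Grade 4 AST/ALT, asymptomatic, judged not clinically significant | DLT | DLT | not a DLT |

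Every row contains a conflict, and no sentence says which text prevails.

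**3. Window against criteria.** Day 1 is the first carboplatin dose and the window is 5 × 7 = 35 days. By the schedule in Sections 4.1 and 7.5, atezolizumab is due on day 15, day 15 + 21 = 36 and day 36 + 21 = 57.

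- Grade 3 for 6 weeks: 6 × 7 = 42 days, more than 35. It cannot be completed in the window whatever the onset.
- Delay of two scheduled atezolizumab doses: toxicity during induction can delay the day-15 dose, and the next is due on day 36. The criterion can be met on day 36 at the earliest, one day after the window closes.
- Grade 4 neutropenia for 14 days: fits only with onset by about day 35 − 14 = 21.
- The 3-week resolution test for an event starting on or after day 15, the first atezolizumab dose, ends on day 15 + 21 = 36 or later.
- Grade 4 or 5 events, febrile neutropenia, thrombocytopenia for 48 hours, bilirubin beyond 48 hours, grade 4 AST/ALT, pneumonitis and colitis can be observed in the window, apart from onsets in its last days for the 48-hour tests.

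**4. Trigger paths.** Exactly two DLTs in six patients can fall in C(6,2) = 15 patterns:

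- none then two: 1 × 3 = 3
- one then one: 3 × 3 = 9
- two then none: 3 × 1 = 3

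The literal wording covers the 9 and omits 6. If one DLT is read as at least one, only none-then-two is omitted, 3 of 15.

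**5. Probabilities.** The protocol gives no DLT rate, so the rate p is an assumption.

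- Two or more of six: 1 − (1 − p)^6 − 6p(1 − p)^5
- Literal path: 3p(1 − p)² × [1 − (1 − p)³]
- At-least-one reading: the literal path plus 3p²(1 − p) + p³

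| p | ≥2 of 6 | Literal path | Share omitted | At-least-one reading | Share omitted |
|---|---|---|---|---|---|
| 10% | 0.114 | 0.066 | 42% | 0.094 | 18% |
| 20% | 0.345 | 0.187 | 46% | 0.291 | 15% |
| 30% | 0.580 | 0.290 | 50% | 0.506 | 13% |

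For p = 30%, the literal path is 0.441 × 0.657 = 0.290.

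**The case against.** Four arguments favour the protocol.

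- **Exceptions override.** A list of events that are not DLTs, placed after the list of DLTs, reads naturally as overriding it. That would settle colitis, pneumonitis and AST/ALT between those two lists. It does not settle the conflict with the bold rule, which counts every grade 4 event while the exceptions run from grade 3 upward. It also leaves the neutropenia, thrombocytopenia and febrile neutropenia rows untouched.
- **Onset reading.** Scoring during the first 5 weeks may mean that onset must fall in the window and that persistence is judged later. That is a fair reading and would remove the timing problem, but the section does not state it.
- **The threshold is stated.** The figure 2/6 is written down and six run-in patients are planned, so investigators would probably report two DLTs in whatever order they came. The gap is therefore in the wording of the path. It remains a gap, because the expansion to six is conditional in Section 4.2 and unconditional in Sections 4.1 and 9.2.
- **Other safeguards.** Section 11.1 requires suspension pending ethics review if the disadvantages of participation may be significantly greater than foreseen. Sections 11.6 and 11.7 set serious-event and SUSAR reporting. Section 6.1.3 cites preliminary data from 90 patients in a study with carboplatin-doublet arms, without additive adverse effects. These points stand and limit the risk to patients. None of them supplies a DLT count.

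**Conclusion.** The concern holds in this form. The conflict between the bold rule and the list is firm: the same patient can be a DLT under one and not under the other. Two criteria cannot be completed by day 35, and others depend on early onset. Read literally, the trigger omits 6 of 15 patterns with exactly 2/6. By probability it omits about 42% to 50% of outcomes with two or more DLTs at assumed rates of 10% to 30%. Under the at-least-one reading this falls to about 18% to 13%. These shares rest on assumed rates and on independent patients with a common rate.

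A reader might infer more than the document supports:

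- That the DLT criteria as a whole cannot be observed in 5 weeks. Most can.
- That the dose-delay criterion must wait until day 57. That is so only if the delayed doses are the second and third; delay of the first two can be seen on day 36.
- That the trigger misses half of the ways to reach 2/6. As a count it misses 40%; half appears only at an assumed rate of about 30%.
- That the trial has no other safety brake, or that 2/6 stops it. The trigger leads to a report and a discussion, and Section 11.1 applies throughout.
- That the efficacy test is compromised. It is not.

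**What to change.** The sponsor should reconcile the bold definition, the DLT list, the exception list, the 5-week window and the synopsis row, so that each event has one classification, it is clear which text prevails, and each criterion can be assessed in the time the protocol allows. The text should say how events that begin in the window but whose duration test ends after it are handled. The wording of the trigger path should be brought into line with the stated 2/6 threshold and the six planned run-in patients, so that every combination of DLTs in the first and second three patients is addressed. Section 9.6 should then point to the reconciled text. Which clinical criteria and which stopping rule apply is for the investigators to decide; none is proposed here.

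The cost is a rewrite of Section 4.2 and the matching synopsis row, probably submitted as a substantial amendment under Section 12.6.2 because it bears on patient safety. Sample size and the efficacy analysis do not change. If criteria that outlast the window are retained, the final DLT count comes later. Whether accrual waits for it is not stated now and should be.

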## 5 Patient selection criteria

- ◆ Signed and written informed consent
- ◆ Age 18 year or older
- ◆ Metastatic or incurable locally advanced lobular breast cancer with **confirmation of the lobular histology and E-cadherin loss or aberrant staining (IHC) on a biopsy of a metastatic lesion**. For patients with a tumor with a mixed-type IDC/ILC or IDC with lobular features a loss or aberrant expression of E-cadherin (IHC) is required [27]
- ◆ Estrogen receptor expression of at least 10% on a metastatic lesion (independent of progesterone receptor expression and HER2 expression)
- ◆ **Metastatic lesion accessible** for histological biopsies (Mandatory biopsies: pre-induction treatment with carboplatin, before start atezolizumab, after 2 cycles of atezolizumab. Optional: upon development of acquired resistance). Biopsies from bone lesions are not permitted. Interval between **last chemotherapy and pre-induction biopsy has to be at least 14 days** (not for endocrine treatment in view of the relatively long half-life). The pre-induction treatment biopsy has to contain **sufficient tumor content (≥100 tumor cells)**; subjects with samples that have insufficient tumor content will require re-biopsy prior to start carboplatin.
- ◆ Evidence of **progression of disease** (either radiological or clinical)
- ◆ Disease progression had to occur after previous endocrine (not necessarily the most recent) therapy in the advanced setting. Patients with an ER-positive tumor must have received **an anti-estrogen (tamoxifen and/or fulvestrant) and at least one aromatase inhibitor** for early breast cancer or metastatic disease.
- ◆ **A maximum of two lines of palliative chemotherapy** for metastatic or incurable locally advanced breast cancer is allowed. HER2-targeting therapy is allowed for the HER2-positive cases. Carboplatin pretreatment is allowed, as long as no progression was observed and the last dose was administered 6 months before starting study treatment.
- ◆ WHO performance status of 0 or 1
- ◆ Absolute lymphocyte count  $\geq 0.5 \times 10^9/L$ , ANC  $\geq 1.5 \times 10^9/L$ , platelets  $\geq 150 \times 10^9/L$ , Hemoglobin  $\geq 6.0$  mmol/L
- ◆ Bilirubin  $< 1.5 \times$  upper limit of the normal range (ULN), except subjects with Gilbert Syndrome; alkaline phosphatase  $< 2.5 \times$  ULN ( $< 5 \times$  ULN in case of liver metastases, and  $< 7 \times$  ULN in case of bone metastases); transaminases (ASAT/ALAT)  $< 3 \times$  ULN (and  $< 5 \times$  ULN in case of liver metastases), **LDH  $< 2 \times$ ULN**.
- ◆ Serum creatinine  $\leq 1.5$  ULN or calculated (Cockcroft-Gault) or measured creatinine clearance  $> 40$  mL/min
- ◆ Evaluable disease or measurable according to RECIST 1.1
- ◆ Subjects with brain metastases are eligible if they have been treated, are not symptomatic and there is no magnetic resonance imaging (MRI) evidence of progression for at least 28 days prior to first dose of study drug administration. There must also be no requirement for immunosuppressive doses of systemic corticosteroids ( $> 10$  mg/day prednisone equivalents) for at least 2 weeks prior to study drug administration
- ◆ No known leptomeningeal disease localization
- ◆ No history of having received other anticancer therapies within 2 weeks of start of the study drug
- ◆ No history of immunodeficiency, autoimmune disease, conditions requiring immunosuppression ( $>10$  mg/day prednisone or equivalent) or chronic infections. Subjects with vitiligo, diabetes mellitus type I, psoriasis not requiring systemic treatment or resolved childhood asthma/atopy would be an exception to this rule. Subjects that require intermittent use of bronchodilators, inhaled steroids, or local steroid injections would not be excluded from the study. Subjects with hypothyroidism stable on hormone replacement, Sjögren's syndrome or conditions not expected to recur in the absence of an external trigger will not be excluded from the study. Adrenal replacement doses  $>10$  mg/day prednisone or equivalent are permitted in the absence of active autoimmune disease
- ◆ No prior treatment with immune checkpoint blockade such as but not limited to anti-PD(L)1, anti-PD-L2, anti-CTLA-4, anti-GITR or CD137/OX40-agonist

- ◆ No live vaccine within 2 weeks prior to start of study, at any time during the study, or within 5 months following the last dose of atezolizumab. Inactivated vaccines are allowed
- ◆ No active other cancer
- ◆ No active hepatitis B (defined as having a positive hepatitis B surface antigen [HBsAg] test at screening) or active hepatitis C. Patients with past hepatitis B virus (HBV) infection or resolved HBV infection (defined as having a negative HBsAg test and a positive antibody to hepatitis B core antigen [anti-HBc] antibody test) are eligible. Patients positive for hepatitis C virus (HCV) antibody are eligible only if polymerase chain reaction (PCR) is negative for HCV RNAActive tuberculosis
- ◆ No history of uncontrolled serious medical or psychiatric illness
- ◆ No known hypersensitivity to Chinese hamster ovary cell products or other recombinant human antibodies
- ◆ Absence of any psychological, familial, sociological or geographical condition potentially hampering compliance with the study protocol and follow-up schedule
- ◆ No current pregnancy or breastfeeding. Women of childbearing potential (WOCBP\*) must use adequate contraceptive protection

\*) "Women of childbearing potential" is defined as any female who has experienced menarche and who has not undergone surgical sterilization (hysterectomy or bilateral oophorectomy) or who is not postmenopausal. Menopause is defined clinically as 12 months of amenorrhea in a woman over 45 in the absence of other biological or physiological causes.

## 6 Therapeutic regimens, dose adjustments and management of toxicity

### 6.1 Atezolizumab

Atezolizumab (MPDL3280A) is a humanized immunoglobulin (Ig) G1 monoclonal antibody consisting of two heavy chains (448 amino acids) and two light chains (214 amino acids) and is produced in Chinese hamster ovary cells. Atezolizumab was engineered to eliminate Fc-effector function via a single amino acid substitution (asparagine to alanine) at position 298 on the heavy chain, which results in a non-glycosylated antibody that has minimal binding to Fc receptors and prevents Fc effector function at expected concentrations in humans. Atezolizumab targets human programmed death-ligand 1 (PD-L1) and inhibits its interaction with its receptors, programmed death-1 (PD-1) and B7.1 (CD80, B7-1). Both of these interactions are reported to provide inhibitory signals to T cells.

Atezolizumab is currently being tested in multiple Phase I, II, and III studies, both as monotherapy and in combination with several anti-cancer therapies (see also Investigator's Brochure). Much of the safety and efficacy data summarized below are from Phase Ia Study PCD4989g, a multicenter, first in-human, open-label, dose-escalation trial evaluating the safety, tolerability, immunogenicity, pharmacokinetics, exploratory pharmacodynamics, and preliminary evidence of biologic activity of atezolizumab administered as a single agent by IV infusion q3w to patients with locally advanced or metastatic solid malignancies or hematologic malignancies. As of 10 May 2014, the clinical database contained preliminary safety data from 412 patients who have received any amount of atezolizumab at doses between 0.01 and 20 mg/kg across multiple tumor types. No dose-limiting toxicities (DLTs) have been observed at any dose level and no maximum tolerated dose (MTD) was established.

Anti-tumor activity including objective responses have been observed in patients with different tumor types, including NSCLC, RCC, melanoma, bladder cancer, CRC, head and neck cancer, gastric cancer, breast cancer, and sarcoma treated with atezolizumab monotherapy in Study PCD4989g. Among 386 evaluable patients enrolled prior to 1 July 2013, there were 47 patients with responses with a median duration of response of 75.7 weeks. The majority of these responses have been durable, with 72.3% (34 of 47 patients) of responses (34 of 47 patients) ongoing as of the clinical cut-off date.

Recently results from the RCC from cohort Study PCD4989g/ NCT01375842 were published[35]. Sixty-three of 70 patients were evaluable for response. The median PFS was 5.6 months (95% CI, 3.9 to 8.2 months), and the median OS was 28.9 months (95% CI, 20.0 months to not reached [NR]). The ORR was 15% (95% CI, 7% to 26%). Analyses of tumor-infiltrating immune cells (ICs) for PD-L1 expression on baseline tumor tissue have been performed for Study PCD4989g/ NCT01375842. Preliminary results from this study suggest that PD-L1 expression on ICs is likely to be associated with response to atezolizumab[36].

As of 2 September 2014, clinical activity analyses have been performed on 21 patients with PD-L1 positive (IC2/3) TNBC in Study PCD4989g who received atezolizumab treatment. Most women had not responded to other treatments and 85% received > 4 prior systemic regimens. Unconfirmed responses were recorded for 5 patients. Two of these patients experienced a complete response and 3 patients experienced a partial response. [31] Arm F from Phase Ib trial GP28328 (TNBC) investigated the combination of atezolizumab with nab-paclitaxel [37]. 24 patients were evaluable for response. The overall response rate (ORR) was 42%, with higher ORR in first line treated patients (67%) compared to third line or higher (29%).

### 6.1.1 Atezolizumab – Adverse Events

Of the 412 treated patients, 97.1% experienced an adverse event (AE) regardless of attribution to atezolizumab. The majority of these AEs were Grade 1 or 2 (NCI CTCAE v4.03). The most frequently observed AEs (occurring in  $\pm 10\%$  of treated patients) included fatigue, nausea, decreased appetite, pyrexia, dyspnea, diarrhea, constipation, cough, headache, back pain, vomiting, anemia, arthralgia, rash, insomnia, asthenia, abdominal pain, chills, pruritus, generalized pain, and peripheral edema.

There were 51 patients (12.4%) who experienced Grade 3 AEs that were assessed as related to study drug by the investigators. The most frequently reported related Grade 3 AEs included fatigue (5 patients [1.2%]), increased AST or ALT (each reported in 4 patients [1.0%]), and asthenia, autoimmune hepatitis, and hypoxia (each reported in 3 patients [0.7%]).

